## Abstract

**Background:**

Lung transplantation (LTx) is the only treatment option for end-stage lung disease. Despite improvements, primary graft dysfunction (PGD) remains the leading cause of early mortality and precipitates chronic lung allograft dysfunction, the main factor in late mortality after LTx. PGD develops within the first 72 hours and impairs the oxygenation capacity of the lung, measured as partial pressure of oxygen (PaO_2_)/fraction of inspired oxygen (FiO_2_). Increasing the PaO_2_/FiO_2_ ratio is thus critical and has an impact on survival. There is a general lack of effective treatments for PGD. When a transplanted lung is not accepted by the immune system in the recipient, a systemic inflammatory response starts where cytokines play a critical role in initiating, amplifying, and maintaining the inflammation leading to PGD. Cytokine filtration can remove these cytokines from the circulation, thus reducing inflammation. In a proof-of-concept preclinical porcine model of LTx, cytokine filtration improved oxygenation and decreased PGD. In a feasibility study, we successfully treated patients undergoing LTx with cytokine filtration (ClinicalTrials.gov; NCT05242289).

**Objective:**

The purpose of this clinical trial is to demonstrate the superiority of cytokine filtration in improving LTx outcome, based on its effects on oxygenation ratio, plasma levels of inflammatory markers, PGD incidence and severity, lung function, kidney function, survival, and quality of life compared with standard treatment with no cytokine filtration.

**Methods:**

This study is a Swedish national interventional randomized controlled trial involving 116 patients. Its primary objective is to investigate the potential benefits of cytokine filtration when used in conjunction with LTx. Specifically, this study aims to determine whether the application of cytokine filtration, administered for a duration of 12 hours within the initial 24 hours following a LTx procedure, can lead to improved patient outcomes. This study seeks to assess various aspects of patient recovery and overall health to ascertain the potential positive impact of this intervention on the posttransplantation course.

**Results:**

The process of patient recruitment for this study is scheduled to commence subsequent to a site initiation visit, which was slated to take place on August 28, 2023. The primary outcome measure that will be assessed in this research endeavor is the oxygenation ratio, a metric denoted as the highest PaO_2_/FiO_2_ ratio achieved by patients within a 72-hour timeframe following their LTx procedure.

**Conclusions:**

We propose that cytokine filtration could enhance the overall outcomes of LTx. Our hypothesis suggests potential improvements in LTx outcome and patient care.

**Trial Registration:**

ClinicalTrials.gov NCT05526950; https://www.clinicaltrials.gov/study/NCT05526950

**International Registered Report Identifier (IRRID):**

PRR1-10.2196/52553

## Introduction

Lung transplantation (LTx) remains the standard option for treating patients with irreversible end-stage pulmonary disease [1]. Of all transplanted organs, the mean 5-year survival is the lowest following LTx [2]. The high mortality is highly associated with primary graft dysfunction (PGD), which arises in the first 72 hours after LTx and can lead to chronic lung allograft dysfunction (CLAD) within the first 3-5 years [3]. The cumulative incidence of these 2 conditions is between 40% and 80%. The fear of PGD leads to a low use rate of donated lungs, with only 20% of donated lungs being used [4].

PGD is reflected in the oxygenation capacity of the lung, measured as the ratio of the partial pressure of oxygen (PaO_2_) to the fraction of inspired oxygen (FiO_2_), which decreases with increasing PGD severity [2]. PGD is diagnosed according to International Society for Heart and Lung Transplantation guidelines [5] if the PaO_2_/FiO_2_ ratio drops below 300 and radiographic infiltrates are present in the lungs, consistent with pulmonary edema. Consequently, increasing the PaO_2_/FiO_2_ ratio following LTx is critical and may directly impact survival.

There is a general lack of effective treatments for both PGD and CLAD. When a transplanted lung is not accepted by the immune system in the recipient, a systemic inflammatory response starts where cytokines play a critical role in initiating, amplifying, and maintaining the inflammation leading to PGD [6]. Cytokine filtration can remove these cytokines from the circulation, thus reducing inflammation. Cytokine filtration devices have been shown in vitro and in vivo during orthotopic heart transplantation and kidney transplantation to target and reduce levels of medium– and low–molecular-weight molecules, such as cytokines, pathogen-associated molecular pattern molecules, and damage-associated molecular patterns [7-9]. Other than our feasibility study (ClinicalTrials.gov; NCT05242289) and a case series using extracorporeal cytokine adsorption therapy as rescue after LTx [10], this tool has not been applied to human LTx.

In this study, we want to test whether cytokine filtration improves outcome if administered in conjunction with LTx, for 12 hours in the first 24 hours following the procedure.

## Methods

### Study Design

The SPIRIT (Standard Protocol Items: Recommendations for Interventional Trials) checklist was used when writing this report [11]. This report is based on protocol version GLUSorb-CIP-V1 dated March 4, 2023. All items from the World Health Organization’s trial registration data set are found at ClinicalTrials.gov (NCT05526950).

### Intervention

The CytoSorb Device (CytoSorb) is a single-use, polymer-based adsorption system for the dialysis of physiological fluids in extracorporeal therapies. It consists of a cartridge, containing a cross-linked divinylbenzene polymer that can be connected to various extracorporeal circuits. Blood is pumped through the CytoSorb cartridge and then returned to the body. The beads bind to a wide range of inflammatory mediators, including cytokines and chemokines. The device has been used in several trials, mostly for cardiac surgery patients [12-17]. The device is Conformité Européene–marked and is to be used within its intended use and indication and according to the manufacturer’s instructions.

The CytoSorb device will be connected for 12 consecutive or nonconsecutive hours within the first 24 hours after the end of the surgery. As participants will be in the intensive care unit during this time, adherence to intervention protocol will be the responsibility of the attending physician and perfusionist. The device may be disconnected and reconnected as necessary for the care of the patient, for example during extubation or mobilization. The participant may also be removed from a clinical investigation by the treating physician, and the intervention discontinued if they find that this is in the best interest of the participant. All other concomitant care and interventions will be according to clinical standard procedures for LTx in Sweden.

### Purpose of the Clinical Investigation

The purpose of this clinical trial is to demonstrate the superiority of cytokine filtration in improving LTx outcome, based on its effects on oxygenation ratio, plasma levels of inflammatory markers, PGD incidence and severity, lung function, kidney function, survival, and quality of life (QOL) compared with standard treatment with no cytokine filtration.

### Study Design and Setting

The investigation is a randomized, parallel group, Swedish national multicenter superiority trial comparing cytokine filtration following LTx to standard treatment with no cytokine filtration. A comparator device will not be used in the control group as there is currently no clinically accepted alternative to achieve cytokine removal from the blood, and thus, the control group will only receive standard LTx treatment. The trial sponsor is Region Skåne and SL is the sponsor representative.

### Inclusion Criteria

The participant must meet the following inclusion criterion:

Eligibility to undergo double LTx at either trial site (Skane University Hospital or Sahlgrenska University Hospital) [18].

### Exclusion Criteria

The participant must not meet any of the following exclusion criteria:

Age <18 yearsPrevious organ transplantationPresence of any conditions at the time of surgery that require immunosuppressive therapy. Immunosuppressive therapy is defined as:Cyclosporine, tacrolimus, everolimus, or sirolimus—minimum 1 month of treatment prior to transplantation and active treatment at the time of transplantation.Any form of antibody-based treatment that is known for having an immunomodulatory effect taken up to 1 week before transplantation.Nonconsent

Patients fulfilling the inclusion criterion and none of the exclusion criteria as shown will be randomized to 1 of the 2 groups. Enrollment will continue until the required sample size is achieved or until the interim analysis.

Any substantial modifications to the protocol after this study begins will be duly communicated to them.

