#### Level of Significance and Power

In the interim analysis (described below), the DSMB will use Pocock stopping boundaries (*P*<.03). Therefore, the 2-sided α value in the final analysis will be *P*=.03. We will use a power of 0.8 (80%).

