#### Sample Size

The power calculation, performed using GPower 3.1 (AdvanSci Research Solutions), is based on superiority analysis assumptions for the primary end point (improved oxygenation ratio, defined as the highest PaO_2_/FiO_2_ ratio measured within 72 h after LTx). Based on data from a cohort of patients undergoing LTx from Skåne University Hospital in Lund from 2011 to 2020, we estimate that the mean PaO_2_/FiO_2_ value in the control group will be approximately 300 (SD 100) mm Hg and that values will be normally distributed. We estimate that the average PaO_2_/FiO_2_ value will be 60 (SD 100) mm Hg higher (effect size) in the treatment group compared with the control group.

The sample size was calculated using a 2-tailed *t* test to compare the PaO_2_/FiO_2_ values in the treatment versus control groups. We will require 52 participants in each group to achieve the power and α level detailed above. We will add 10% of the required sample size to account for possible dropouts, withdrawal of consent, or mortality in the first 72 hours. Thus, we aim to recruit 58 patients in each group to a total of 116 participants. With this number of participants, we estimate that all secondary outcome variables will have a power of at least 80% at an α level of .05.

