#### Interim Analysis

The DSMB will perform an interim analysis of the primary outcome after at least 30 participants for each group have undergone LTx and reached the intervention period and the 72-hour time point has been passed for the 30th participant in each group. The DSMB will use Pocock stopping boundaries (*P*<.03) as the statistical limit to guide its recommendations regarding early termination of the trial on the basis of rejecting the null hypothesis. If the *P* value for the primary outcome is below .03 at the interim analysis, then a decision will be taken by the trial management team to either stop the trial early or to continue recruitment. This has been accounted for in the sample size calculation above, and no additional adjustments for multiple testing are necessary.

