#### Replacement

Participants who withdraw or are withdrawn from this study or who are lost to follow-up will not be replaced. If a participant’s transplantation surgery is cancelled or rescheduled after they are randomized (they will keep the randomization number if later transplanted), new participants will continue to be randomized until the target number of participants has completed their transplantation surgery.

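### The enrolment sentence under Exclusion Criteria ends recruitment at the interim analysis without condition, contradicting the interim rule and the sample-size plan

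*Protocol article*

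**What the plan says.** All references are to the protocol article.

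- **Exclusion Criteria** states when enrolment ends: "Enrollment will continue until the required sample size is achieved or until the interim analysis". The two end points are joined by an unqualified alternative.
- **Interim Analysis** sets the timing, "after at least 30 participants for each group have undergone LTx and reached the intervention period", with the 72-hour point passed for the 30th patient in each group. If the primary-outcome P value is below .03, "then a decision will be taken by the trial management team to either stop the trial early or to continue recruitment". No action is attached to a P value of .03 or more.
- **Level of Significance and Power** provides for a later analysis: "Therefore, the 2-sided α value in the final analysis will be" .03, with 80% power.
- **Sample Size** requires 52 participants per group and, with 10% added, recruits 58 per group and 116 in total.
- **Results** expects enrolment to last 3.5 years at 30 to 50 participants per year.

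**The concern.** The interim comes well before the recruitment target. If reaching the interim is by itself enough to end enrolment, the required sample size can never be the event that closes recruitment, and the final analysis at .03 has no second stage of patients to analyse. A trial that did not cross the boundary at the interim would then end there, underpowered and probably inconclusive.

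The article does not simply leave this detail to the full protocol. It states an enrolment rule, and that rule does not agree with its own interim rule.

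**Working it through.** **1. Inputs.** From Sample Size: "value in the control group will be approximately 300 (SD 100) mm Hg" and "value will be 60 (SD 100) mm Hg higher (effect size) in the treatment group", so the standardised difference is d = 60/100 = 0.6, tested with a two-tailed t test. From Level of Significance and Power: two-sided α = .03, power 80%. From Interim Analysis: n = 30 per group at the earliest.

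**2. Reproducing the plan's figure.** Power comes from the noncentral t distribution with 2n − 2 degrees of freedom and noncentrality d·√(n/2).

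- n = 51 per group: power 79.5%.
- n = 52 per group: noncentrality 0.6·√26 = 3.06, power 80.3%. This is the smallest n that reaches 80%, as the article states.
- Dropout allowance: 52 × 1.10 = 57.2, or 52/0.90 = 57.8. Both round up to 58 per group, 116 in total, as stated.

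**3. Enrolment ending at the earliest interim.** The same test with n = 30 has noncentrality 0.6·√15 = 2.32.

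| Patients per group | Power, t test | Power, normal approximation | Chance of missing the effect (t test) |
|---|---|---|---|
| 30 | 54.2% | Φ(2.324 − 2.170) = 56.1% | 45.8% |
| 52 | 80.3% | Φ(3.059 − 2.170) = 81.3% | 19.7% |

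The chance of missing the effect rises by a factor of 45.8/19.7 ≈ 2.3. Patients not enrolled: 116 − 2 × 30 = 56.

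**4. Sensitivity.** Thirty per group is a minimum, so 54% is the lowest figure that this reading gives. An interim at 45 per group would give 73.8%. Testing 30 per group at .05 instead of .03, as if only one look had been planned, would give about 63%, still well below 80%.

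**5. Enrolment continuing as the Interim Analysis section implies.** With looks at 30 and 52 per group and P<.03 at each, a bivariate normal calculation gives overall power of about 83% and two-sided type I error of about .049. With a final look at all 58 per group, the figures are about 87% and .051. The planned design therefore performs roughly as intended, provided that the second stage takes place.

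**6. Enrolment period.** At 30 to 50 participants per year, 3.5 years yields 105 to 175 patients, which fits 116. Sixty patients would need only 60/50 = 1.2 to 60/30 = 2 years.

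**The case against.** The strongest reply is that the sentence is shorthand. On the literal reading its first end point could never operate; only a reading such as stopping under the interim rule gives both end points meaning. The final-analysis α, the target of 116, the option to continue recruitment and the 3.5-year timeline all presuppose continuation. The specific statistical sections would naturally override a loose sentence among the eligibility criteria. The article also condenses a clinical investigation plan that is not shown, and Site Monitoring says that conduct is checked against that plan. This reply largely stands: it makes the defect one of wording, with the intended design recoverable. It does not make the sentence correct.

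Some stronger readings are tempting but not supported:

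- A reader might infer that the trial will in fact stop at 30 per group whatever the interim shows. The sentence does not say so outright, and the statistical sections point the other way.
- A reader might take the Replacement section, where "new participants will continue to be randomized until the target number of participants has completed their transplantation surgery", as a third, conflicting stopping rule. It deals with surgery cancelled or rescheduled after randomisation and is not a general rule. Its wording merely assumes the full target.
- A reader might say that power is halved. It falls to about two thirds of the planned figure (54/80 ≈ 0.68); what more than doubles is the risk of missing the effect.
- A reader might conclude that enrolment must pause, or must continue, while the DSMB reviews the interim data. The documents do not settle this, and correcting the contradiction does not require it.

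**Conclusion.** The point holds as an internal contradiction in a stated rule. The enrolment sentence under Exclusion Criteria is wrong as written and disagrees with Interim Analysis, Level of Significance and Power, Sample Size, and the timeline in Results.

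The power loss worked out above is conditional. It applies only if the sentence is followed literally and the interim takes place at its minimum size, with the plan's own difference, SD and α and no loss of primary-outcome data. It measures what the sentence would cost if applied and does not predict what the trial will do. The correction is worth making because it is cheap and because the length of enrolment should not be open to interpretation once an interim result exists.

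**What to change.** Reword the sentence under Exclusion Criteria so that enrolment runs to the required sample size unless the trial is stopped early, either under the rule in the Interim Analysis section or by the DSMB for safety as the Data Safety Monitoring Board section already allows. If the full clinical investigation plan carries the same sentence, correct it there too. Interim Analysis and Replacement need no change on this account.

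The cost is one sentence. Sample size, α and interim timing are unaffected.

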### Clinical Investigation Objectives

#### Primary Objective

The primary objective is to determine whether cytokine reduction by cytokine filtration leads to improved oxygenation in patients undergoing LTx.

#### Secondary Objective

The secondary objective is to determine whether cytokine reduction by cytokine filtration improves levels of plasma inflammatory markers (including cytokines), lung infiltrates and oedema, arterial blood gas measures, incidence and severity of PGD, need for norepinephrine, mortality, lung diffusion capacity, spirometry measures, acute rejection episodes, chest computed tomography (CT) findings, CLAD, kidney function, and QOL in patients undergoing LTx.

#### Safety Objective

The safety objective is to determine the number of adverse events and plasma levels of immunosuppressant drugs following cytokine filtration in patients undergoing LTx.

#### Exploratory Objective

The exploratory objective is the collection of lung tissue, blood, bronchoalveolar lavage fluid samples and, when available, explanted tissue from recipients for future exploratory analyses of cytokines and immune cells in patients undergoing LTx with and without cytokine filtration.

### Study Population

This study’s population will consist of a representative group (n=116) of patients with de novo double lung transplants in Sweden who fulﬁll the requirements according to the inclusion and exclusion criteria stated above.

### Outcomes

#### Primary Performance End Point

The primary end point is the oxygenation ratio, defined as the highest PaO_2_/FiO_2_ ratio within 72 hours after LTx.

#### Secondary Performance End Points

The secondary end points are (1) plasma levels of inflammatory markers: interleukin (IL)-10, IL-1β, soluble IL-2 receptor, IL-6, IL-8, and tumor necrosis factor α before and immediately after transplantation and at 6, 12, 24, 48, and 72 hours after transplantation and C-reactive protein and white blood cells before and immediately after transplantation and at day 1, 2, and 3 after transplantation; (2) infiltrates and oedema measured by chest x-ray or CT scan of the thorax at day 1, 2, and 3 after transplantation; (3) highest daily arterial blood gas measurements recorded on day 1, 2, and 3 after transplantation, as a measure of lung function; (4) PGD severity as evaluated per standard clinical procedures using a rating scale from 0 to 3 on day 1, 2, and 3 after transplantation, as a measure of lung function; (5) presence of any grade of PGD on day 1, 2, and 3 after transplantation, as a measure of lung function; (6) total dose of norepinephrine administered in the first 72 hours; (7) mortality up to 48 months after transplantation; (8) lung diffusion capacity, measured by carbon monoxide diffusion, at 6, 12, 24, and 48 months after transplantation, as a measure of lung function; (9) forced expiratory volume, forced vital capacity, and total lung capacity measured by spirometry at 1, 3, 6, 12, 24, and 48 months after transplantation, as a measure of lung function; (10) occurrence of any acute rejection episodes (clinically treated and/or biopsy verified) up to 48 months after transplantation, as a measure of lung function; (11) chest CT findings at 1, 3, 6, 12, 24, 36, and 48 months after transplantation; (12) the presence of any CLAD and CLAD subtypes up to 48 months after transplantation, as a measure of lung function; (13) kidney function evaluated by measurement of serum creatinine levels; calculated glomerular filtration rate and need for renal replacement therapy on day 1, 2, and 3 and at 1, 3, 6, 9, 12, 24, and 48 months after transplantation; urea levels on day 1, 2, and 3 after transplantation; and iohexol-clearance at 3, 6, 9, 12, 24, 36, and 48 months after transplantation; and (14) QOL evaluated by the 36-Item Short Form Health Survey at 24 and 48 months after transplantation.

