#### Statistical Design, Method, and Analytical Procedures

All statistical analyses will be performed by an independent statistician. Treatment allocation will remain concealed during the initial analysis, with the 2 groups labelled as “group A” and “group B,” ensuring a blinded statistical analysis. All statistical tests will be 2-sided. The distribution of continuous variables will be determined by visual inspection of histograms and quantile-quantile plots. The primary outcome will be based on the mean highest PaO_2_/FiO_2_ ratio within the first 72 hours (a continuous variable). Differences between treatment groups in the mean highest PaO_2_/FiO_2_ ratio within the first 72 hours will be compared using a multivariate linear regression model adjusted for, at minimum, the stratification variables (site, age, and gender). Continuous variables, ordered categorical variables, and binary variables measured over time will be compared using mixed models for repeated measures. The distribution of the data will be checked using quantile-quantile plots, and if the data are skewed, then a generalized linear mixed effects model with the appropriate distribution will be used. A random intercept will be applied at the patient level. We will check model assumptions for each model. Kaplan-Meier survival analysis will be performed for mortality data up to 48 months after transplantation. Median QOL scores from each instrument (ordinal variables) will be compared using the Mann-Whitney *U* test at each time point. Subgroups for analysis shall be described in detail in the statistical analysis plan.

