## Discussion

### Overview

Intolerance to a new lung, which leads to PGD, begins already during transplantation and is driven by intense inflammation caused by circulating cytokines [6]. Cytokine filtration can remove the cytokines that lead to intolerance and subsequent PGD from the circulation, thus reducing inflammation, and could therefore improve outcomes in LTx. However, the effectiveness of the CytoSorb device in LTx has yet to be established. Other than our feasibility study (NCT05242289) and a smaller case series that was rescued with extracorporeal cytokine adsorption therapy following LTx [10], this tool has not been applied to human LTx by any clinic within our network or in any trials that are registered at ClinicalTrials.gov or other registries. Therefore, this clinical investigation is justified and relevant as it will establish the effectiveness of cytokine reduction by cytokine filtration using the CytoSorb device in improving lung function following LTx, an area where there is a high unmet need. The clinical investigation is designed to evaluate whether the investigational device is suitable for the purposes and populations for which it is intended within LTx, namely for removal of cytokines in these patients.

Following LTx, the anticipated clinical benefits of cytokine filtration using the CytoSorb device in LTx are reduced severity and incidence of PGD, improved lung function, improved kidney function, improved hemodynamic stability, and reduced mortality.

In a preclinical study of LTx carried out by Ghaidan et al [28], pigs were randomized 1:1 to undergo LTx with or without cytokine filtration with the CytoSorb device during the first postoperative period and followed for 3 days after transplantation. Cytokine filtration significantly improved lung function, evidenced by increased PaO_2_/FiO_2_ ratio, and reduced the incidence of histologically confirmed PGD. Treated animals also had lower levels of inflammatory biomarkers in plasma and bronchial alveolar lavage fluid, lower levels of lymphocytes, neutrophils, and total white blood cells; required less inotropic support; and experienced greater lactate clearance postoperatively.

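### PGD incidence is a named objective, but its only end point is daily presence in a repeated-measures model, so a filter that merely shortens PGD can appear to reduce incidence

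*Protocol article*

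**What the plan says.** Incidence of PGD is named beside severity in three places of the protocol article: Purpose of the Clinical Investigation ("PGD incidence and severity"), Secondary Objective ("incidence and severity of PGD") and, as an anticipated benefit, the Overview of the Discussion ("reduced severity and incidence of PGD").

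Under Secondary Performance End Points, severity has its own item (4), a 0-3 grade on each of the three days. Incidence is left with item (5): "presence of any grade of PGD on day 1, 2, and 3 after transplantation".

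Statistical Design, Method, and Analytical Procedures gives one rule for all such variables: "Continuous variables, ordered categorical variables, and binary variables measured over time will be compared using mixed models for repeated measures". It adds: "A random intercept will be applied at the patient level". The article defines no per-patient variable for having developed PGD within the risk window, which the Introduction describes with the words "which arises in the first 72 hours after LTx".

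**The concern.** Incidence is a count of patients: how many develop PGD. Daily presence is a count of patient-days, and it falls if fewer patients develop PGD or if the same number recover sooner. An overall arm effect from a repeated-measures model of daily presence cannot separate the two.

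This matters here because a duration-only effect is plausible. The Overview says that the process leading to PGD starts during transplantation, while the Intervention section connects the device only after surgery has ended, for 12 of the first 24 hours. If the filter speeds recovery without preventing onset, a significant result on end point (5) could be reported as lower incidence, on a named part of the superiority purpose, although just as many patients developed PGD.

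**Working it through.** **The plan's own figure.** The article states no figure for PGD incidence. Its sample size reproduces: standardized difference 60/100 = 0.6, two-sided alpha 0.03, power 0.80. The noncentral t calculation gives 52 per group (power 0.803). Adding 10% gives 52 × 1.10 = 57.2, rounded up to 58 per group. The checks below use 58 per arm and the two-sided .05 that the article names for secondary outcomes.

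**Reading the end point.** Item (5) repeats the day-by-day form of items (2) to (4). Where the same list means a cumulative outcome, as for acute rejection in item (10) and CLAD in item (12), it gives a period running up to 48 months. Item (5) is therefore most naturally a status recorded on three days, which brings it under the rule that "binary variables measured over time will be compared using mixed models for repeated measures".

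**What daily presence measures.** For the three-day average the identity is exact:

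mean daily presence = (proportion ever with PGD) × (mean PGD days among those affected) / 3.

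**Main scenario (assumed rates, PGD starting on day 1).** Incidence is 50% in both arms; mean duration is 2.5 days (control) and 1.5 days (treated).
- Control: 0.50 × 2.5 / 3 = 0.417.
- Treated: 0.50 × 1.5 / 3 = 0.250.
- A test of mean daily presence per patient, a stand-in for the mixed model, rejects in 65.7% of 4,000 simulated trials. The per-patient test of any PGD rejects in 4.8%.
- Refitting with a random-intercept logistic model gives about 55-61%, against 6-7% for the per-patient test.

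**Range of assumed rates.** The Introduction gives 40% to 80% for PGD and CLAD together, with no PGD-only rate, so that span was used as an assumption. With PGD starting on day 1, the mean duration is 2.75 days in control (25% of cases last 2 days, 75% last 3) and 1.55 days in treated (60%, 25% and 15% last 1, 2 and 3 days). Each row is 300 simulated trials.

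| Ever PGD, both arms | Mean daily presence, control / treated | Random-intercept logistic rejects | Per-patient test rejects |
|---|---|---|---|
| 40% | 0.40 × 2.75/3 = 37% / 0.40 × 1.55/3 = 21% | 82% | 4% |
| 60% | 55% / 31% | 87% | 5% |
| 80% | 73% / 41% | 99.7% | 6% |

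With equal incidence and equal duration the same logistic model rejected in 7% to 10%, so it is somewhat liberal as fitted. That does not explain 82% or more.

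**When the two analyses agree.** Incidence 60% against 35% with the same duration pattern in both arms: the logistic model rejects in 73% and the per-patient test in 78%, in the same direction.

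**The case against.** **It belongs in the statistical analysis plan.** The article condenses a longer protocol and refers to a separate analysis plan. Its modelling rule is generic and names no contrast, time coding or treatment-by-day term. That carries weight for the details: nothing in the article says that a day-averaged effect will be reported as incidence, and a reader should not infer that it certainly will be. But the objective, the end point and the class of model are all fixed here. An analysis plan that follows them inherits the mismatch, and one that adds a per-patient variable adds an end point.

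**Item (5) could mean at any time over days 1-3.** That reading would remove the problem. The parallel with items (2) to (4) and the repeated-measures rule speak against it. If both readings are open, they lead to different tests and the text still needs settling.

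**A day-1 contrast would do.** In the simulations PGD always starts on day 1, so presence on day 1 equals incidence, and a model with day terms could supply that contrast. This is correct, but the article names no such contrast, and with later onset it would no longer equal incidence.

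**The stronger reading.** A reader might infer that the planned analysis would also hide a true fall in incidence, with only about 5% power. The documents do not support that. The figure comes from the stand-in test with 50% against 30% incidence and mean durations 1.8 and 3 days (0.50 × 1.8/3 = 0.30 and 0.30 × 3/3 = 0.30). Random-intercept logistic fits of that scenario rejected in anything from 8% to 92%, depending on how the random-intercept variance was handled, and a joint test of arm and arm-by-day in about 100%. Two other patterns with equal mean presence diverged: at 60% against 40% ever, the logistic model rejected in 62% and the per-patient test in 58%; at 80% against 55%, the logistic model favoured treatment in only 13%, with a median log odds ratio of +1.4, against 80% for the per-patient test. Masking can occur, but its size cannot be stated in general. It also requires the filter to lengthen PGD in the remaining cases, which nothing in the article suggests.

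**Conclusion.** The point holds for the direction in which daily presence overstates an effect on incidence. The protocol names incidence, fixes daily presence as its end point and assigns a model whose overall arm effect responds to duration as well as to onset. With equal incidence of 50% and mean durations 2.5 against 1.5 days, the planned type of model rejects in roughly 55-65% of trials where a per-patient test rejects in about 5%.

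This rests on assumed rates, on onset by day 1 and on the overall arm effect being the quantity reported. The percentage moves with the way durations are spread around their means and with the estimation of the random-intercept variance: other fits of duration-only effects ran from 50% to 97%, and a pattern of very short or full three-day episodes can pull it lower. The direction of the problem does not depend on the exact figure.

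The importance is minor to moderate. One of 14 secondary end points is affected; the primary analysis and the sample size are not. Daily presence remains a valid description of the course of PGD, as long as it is not read as incidence.

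**What to change.** - In item (5), define PGD incidence once per patient: grade 1 or higher on any of days 1, 2 or 3, derived from the daily grades already collected under Medical Chart Review.
- In the analysis section, compare it between arms with a single logistic regression or adjusted risk difference, using site, age and gender.
- State how deaths before 72 hours count in this variable.
- Keep the daily presence and grade analyses, labelled as the course of PGD.

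The cost is one derived variable, a few sentences and one more secondary analysis; no new data are needed. The per-patient variable carries no information on duration, which the daily grades still supply. Its power at 58 per arm is modest for moderate effects: about 58% for 60% against 40%, 78% for 60% against 35%, and 83% for 80% against 55% (all assumed rates).
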